## Abstract

**Introduction:**

An acute hospital admission is a stressful life event for older people, particularly for those with cognitive impairment. The hospitalisation is often complicated by hospital-associated geriatric syndromes, including delirium and functional loss, leading to functional decline and nursing home admission. Hospital at Home care aims to avoid hospitalisation-associated adverse outcomes in older patients with cognitive impairment by providing hospital care in the patient’s own environment.

**Methods and analysis:**

This randomised, non-blinded feasibility trial aims to assess the feasibility of conducting a randomised controlled trial in terms of the recruitment, use and acceptability of Hospital at Home care for older patients with cognitive impairment. The quality of care will be evaluated and the advantages and disadvantages of the Hospital at Home care programme compared with usual hospital care. Eligible patients will be randomised either to Hospital at Home care in their own environment or usual hospital care. The intervention consists of hospital level care provided at patients’ homes, including visits from healthcare professionals, diagnostics (laboratory tests, blood cultures) and treatment. The control group will receive usual hospital care. Measurements will be conducted at baseline, during admission, at discharge and at 3 and 6 months after the baseline assessment.

**Ethics and dissemination:**

Institutional ethics approval has been granted. The findings will be disseminated through public lectures, professional and scientific conferences, as well as peer-reviewed journal articles. The study findings will contribute to knowledge on the implementation of Hospital at Home care for older patients with cognitive disorders. The results will be used to inform and support strategies to deliver eligible care to older patients with cognitive impairment.

**Trial registration number:**

NTR6581; Pre-results.

Strengths and limitations of this studyThis study addresses the feasibility of Hospital at Home care in patients with cognitive impairment, a patient population that is often excluded from participation in scientific research.A process evaluation facilitates the investigation of factors that influence the experiences and perceptions of all persons involved in Hospital at Home care.Stakeholders were involved in the development of the design of the study which will support the implementation of Hospital at Home care and a future trial.Because of a limited sample size due to the study being centred on feasibility, results will not show effectiveness of Hospital at Home care compared with usual hospital care.

## Introduction

### Background

An acute hospital admission is a stressful life event, particularly for older people. In addition to the stress of an acute illness, the hospital admission itself contributes to this stress.^1^ Older hospitalised patients are often deprived of sleep, and they spend an average of 20 of every 24 hours in bed, they become poorly nourished, and experience sensory deprivation or overstimulation, resulting in confusion.^2–5^ These adverse effects of hospitalisation contribute to the occurrence of geriatric conditions, such as delirium, functional decline, falls, incontinence, hospital acquired infections and pressure injuries.^6–9^ Adverse effects of hospitalisation occur more easily in older people, particularly in those who are already frail, a growing portion of the worldwide ageing population.^10 11^ Frailty is a state of increased vulnerability to external stressors resulting from ageing-associated declines in reserve and function across multiple physiological systems.^10^ Cognitive impairment (ie, dementia) is an important contributor to frailty in older people.^12^ Cognitively impaired older people are more likely to become hospitalised and once admitted, they experience longer stays than their peers without cognitive impairment.^13–15^ The combination of hospitalisation and cognitive impairment in older people is associated with further functional and cognitive declines and higher mortality rates, and it leads to more discharges to long-term care facilities.^16 17^ The prevalence and worldwide burden of cognitive impairment will continue to increase as the average life expectancy increases.^18^ The total number of people with cognitive impairment is estimated to be 75.6 million in 2030 and will nearly triple in 2050 to 135.5 million.^19^ An increase in the number of hospital admissions of older people with cognitive impairment and an increase in number of hospitalisation-associated adverse outcomes are therefore to be expected.

Besides adverse outcomes of hospitalisation, many older people and their caregivers do not necessarily desire a hospital admission in case of an acute illness or exacerbation of a chronic illness. Fried *et al* (2000) have studied the preferences of community-dwelling persons 65 years of age and older who were hospitalised with a primary diagnosis of congestive heart failure, chronic obstructive pulmonary disease (COPD) or pneumonia. The authors reported that over 50% of older patients preferred to receive hospital treatment at home, because they felt that their homes were more comfortable.^20^ In the treatment preferences of seriously ill patients aged 60 years and older, the likelihood of cognitive and functional impairment as an adverse outcome of the treatment was weighed in the decision-making process. There was a substantial decrease in the number of participants who opted for treatment if the likelihood of impairment after treatment was 50% or higher.^21^

Hospital at Home care could provide an effective alternative to inpatient care for a select group of elderly patients now requiring hospitalisation. Hospital at Home care is coordinated, multidisciplinary care in the homes of people who would otherwise be admitted to the hospital. Hospital at Home care is an accepted alternative to inpatient hospital level care in several countries (eg, the USA, Italy and the UK) but not yet in the Netherlands.^22^ Since the 1990s, Hospital at Home has been evaluated in (older) persons with various acute medical conditions, such as heart failure, exacerbations in COPD and infections (eg, cellulitis, pneumonia).^22^ In systematic reviews comparing alternative strategies to inpatient hospitalisation, lower or equal mortality rates and return hospitalisation rates (ie, subsequent admissions after discharge) were found for Hospital at Home care, there was a lower incidence of delirium, and there was a positive effect on patient and caregiver satisfaction.^22–24^ Only one completed trial conducted in Italy included 109 patients with cognitive impairment (ie, dementia), Tibaldi *et al* reported a positive effect of a Hospital at Home intervention on behavioural disturbances and caregiver stress in patients with dementia.^25^ Results of a still ongoing trial including people with i.a. cognitive impairment in the UK, will follow in the near future.^26^

Whether Hospital at Home care provides a suitable alternative with regard to other outcomes as patient satisfaction, quality of care, hospitalisation-associated adverse events and costs in older people with cognitive impairment remains unclear and further research is needed. Therefore, our primary aim is to investigate the feasibility of a Hospital at Home care programme for older patients with cognitive impairment in terms of the patient recruitment, use and acceptability, and second to investigate the advantages and disadvantages of Hospital at Home care compared with usual hospital care from different perspectives.

Objectives of this study are the following:To assess the participation rate of the Hospital at Home trial among patients 65 years and older with cognitive impairment, acute illness and emergency hospital admission. What are the reasons for non-participation?To assess the potential advantages and disadvantages of Hospital at Home care and usual hospital care for the patients, caregivers and Dutch medical health system.To assess the feasibility of Hospital at Home care in terms of the quality of care with regard to geriatric syndromes, institutionalisation, mortality, total days with urinary catheter, length of stay (in the hospital or in Hospital at Home care) and timing/intensity of the contact with healthcare professionals.

## Methods and analysis

### Trial design

The design is a randomised controlled feasibility trial and will use a process evaluation. This study will be conducted at the medical emergency department (ED) of the academic hospital of the University Medical Center of Groningen in the Netherlands and will evaluate cognitively impaired older patients who are in need of acute hospital care. Figure 1 shows the trial design summary. Participants will be randomised to either Hospital at Home care or usual hospital care in a 4:1 ratio, respectively. Patients will be randomised using a computerised random number generator (http://www.randomization.com), including block randomisation.

**Figure 1 F1:**
[figure not shown]
Flow chart of trial design summary

An independent research nurse who is not involved in the patient care will complete the baseline assessment and allocate the participants (using sealed sequenced envelopes) into the Hospital at Home care (intervention) or usual hospital care group (control). The research nurse will not be aware of the randomisation method. The participants, healthcare professionals and research staff will not be blinded to the intervention. The reporting of the design of this trial protocol is in accordance with the SPIRIT (Standard Protocol Items: Recommendations for Interventional Trials) 2013 statement for clinical trial protocols.^27^

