### Study population

Patients 65 years of age and older who are admitted to the medical ED will be identified by the ED staff as potential eligible patients. Subsequently, the ED staff will inform the research nurse. The research nurse will complete the eligibility criteria checklist (table 1). The research nurse will ask the patient and their informal caregiver (ie, partner, child, relative, friend) for their willingness to participate in the study and to provide written informed consent. The patient and informal caregiver will need to both sign the informed consent form before the patient can participate in the H@H trial.

**Table 1 T1:** Patient eligibility criteria for participation in Hospital at Home trial

Inclusion criteria	Exclusion criteria
Age 65 years of age and older Cognitive impairment, that is, dementia, delirium or other cause of cognitive impairment, and either Previously diagnosed or documented in the medical records or Identified by the ED clinician (eg, with the 4AT test and/or six-item cognitive impairment test)^42–44^ Presented at the ED with a defined acute illness Required hospital admission, according to the attending ED physician but not expected to require emergency interventions, Modified Early Warning Score ≤2 points^45–47^ Living in hospital’s catchment area (<25 km) Informal caregiver is present and able to understand and perform instructions and consented to participate in the trial Home suitable for Hospital at Home care (available informal caregiver, running water, adequate heating, safety)^44^	Previously enrolled Hospitalised within the 7 days preceding ED presentation Nursing home residents or awaiting a nursing home place on an active waiting list (excluding so-called sleeping waiting list candidates)^27^ Additional care needed: Required surgical assessment Suspected acute coronary syndrome or cardiac arrythmia^45^ Dialysis dependent patients^45^ Expected terminal events^45^ or in need of diagnostic or palliative care due to oncological or haematological illness

ED, emergency department.

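### The unblinded research-nurse role that screens and recruits also opens the allocation envelopes from a blocked 4:1 list, so concealment rests on fragile safeguards

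*Protocol article*

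**What the plan says.** Trial design, in Methods and analysis, sets the ratio: "Participants will be randomised to either Hospital at Home care or usual hospital care in a 4:1 ratio, respectively". The list comes from a computerised generator, "including block randomisation", at the emergency department (ED) of one hospital.

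The same section describes the allocator as "An independent research nurse who is not involved in the patient care", who "will complete the baseline assessment and allocate the participants (using sealed sequenced envelopes"). It adds a safeguard: "The research nurse will not be aware of the randomisation method". It also states: "The participants, healthcare professionals and research staff will not be blinded to the intervention".

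Under Study population, patients "will be identified by the ED staff as potential eligible patients", and the ED staff then inform the research nurse. After that, "The research nurse will complete the eligibility criteria checklist" and asks patient and caregiver for consent. Study procedures puts consent, cognitive tests and baseline assessment before randomisation.

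**The concern.** Allocation concealment is meant to ensure that whoever decides on entry cannot know the next arm. Here one role judges eligibility, makes the approach and opens the envelope, and so learns each result as it arises. Withholding the randomisation method does not withhold its output. Someone who opens a sequence of envelopes at a single site can come to see that controls are about one in five and fairly evenly spaced.

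Two criteria in Table 1 leave clear room for judgement: whether the caregiver can understand and carry out instructions, and whether the home is suitable, including its safety. If the next arm is foreseen, these judgements, or the way in which the study is offered, could shift with it.

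Both feasibility criteria are exposed. A patient judged unsuitable leaves the denominator of the participation rate, and the manner of the approach affects the numerator. The Feasibility section also calls the study feasible if quality of care at home is non-inferior to usual care. That compares arms, and selective entry could bias it.

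**Working it through.** **1. Who does what**

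| Step | Role | Section |
|---|---|---|
| First identification | ED staff | Study population |
| Eligibility checklist | Research nurse | Study population |
| Consent approach | Research nurse | Study population |
| Baseline assessment | Research nurse | Trial design |
| Opening of envelope | Research nurse | Trial design |

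Only the first step lies outside the role. Nothing in the article separates the recruiter from the allocator.

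**2. Expected size (Sample size section).** 1900 × 0.15 = 285 eligible per year, and 285 × 0.50 = 142.5, rounded up to the stated 143. The plan's figure is reproduced. At 4:1 the control arm would be 143 / 5 = 28.6, about 29 patients. The article does not state that number.

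**3. Allocations that could be certain in advance.** Assumptions: fixed blocks, and a guesser who knows the block size, the block boundaries and all earlier allocations. The article states none of the block details. An allocation is certain once all remaining places in its block belong to one arm. For a block with h Hospital at Home and c control places, the expected number of certain places is

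h / (c + 1) + c / (h + 1)

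The first term counts places certain to be Hospital at Home, the second those certain to be control.

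| Block | Expected certain places | Share | Of 143 |
|---|---|---|---|
| 5 (4:1) | 4/2 + 1/5 = 2.20 | 44.0% | about 63 |
| 10 (8:2) | 8/3 + 2/9 = 2.89 | 28.9% | about 41 |
| 15 (12:3) | 12/4 + 3/13 = 3.23 | 21.5% | about 31 |
| 20 (16:4) | 16/5 + 4/17 = 3.44 | 17.2% | about 25 |

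Full enumeration of the blocks gives the same shares. Five is the smallest block that can hold a 4:1 ratio, so 44% is the ceiling. Most of it is certainty of Hospital at Home: with blocks of 5, 2/5 = 40% of all allocations, against 0.2/5 = 4% that are certain controls.

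**4. Average guessing accuracy.** Without block knowledge, always naming Hospital at Home is right 80% of the time. With blocks of 5 known, the guesser names the likelier arm and tosses a coin on a tie. If the control falls in place 1, 2 or 3, the guesser gets 4 of 5 right. If it falls in place 4 or 5, the expected number is 4.5. The mean is (3 × 4 + 2 × 4.5) / 5 = 4.2 of 5, or 84.0%. Enumeration gives 82.4% for blocks of 10, 81.8% for 15 and 81.4% for 20. The gain over 80% is at most 4 percentage points.

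**The case against.** A reader might infer that upcoming allocations can in fact be guessed, or that 44% of them are known. The article does not support this. It keeps the nurse unaware of the method, gives no block size and does not say that blocks are fixed. Seeing a ratio of about 4:1 reveals neither the length of a block nor where it begins, and nothing here shows how quickly either could be learned. The shares above are ceilings, and the average gain in guessing accuracy is small.

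Nor can early opening of envelopes by the recruiter be read into the text. Custody between uses is not described, the envelopes are sealed and sequenced, and consent and baseline assessment come first. A condensed article may leave block size and custody to the full protocol, so their absence is no fault, and varying blocks may already be in use.

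Discretion is also limited. ED staff identify candidates, the need for admission is the ED physician's decision, and age, early warning score and distance are objective. The nurse is outside patient care, and the role may be filled by several people, each of whom would see less of the sequence. The trial disclaims effectiveness, its stated analysis is descriptive, and it records reasons for non-participation, which makes part of any selection visible.

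All this limits the size of the concern. It does not answer the structural point: the article itself fixes that the recruiting role opens the envelopes and so sees the past sequence. Placing consent before the envelope guards against reacting to a known result, not against anticipating the next one. The average accuracy is also an incomplete measure, because steering needs only particular moments of certainty. A descriptive summary does not remove selection bias.

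**Conclusion.** The point holds as a risk that is cheap to reduce. Recruitment and allocation sit in one unblinded role, and concealment rests mainly on sealed envelopes and on that role's unawareness of the method.

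The size depends on block details that the article does not give. If blocks were fixed and inferred, at most 44%, 29% or 22% of allocations would be certain in advance with blocks of 5, 10 or 15, and average guessing accuracy would be 82% to 84% instead of 80%. With unknown or varying blocks the exposure would be smaller. The documents do not show that any allocation would be foreseen, and neither the direction nor the amount of any bias can be derived from them.

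**What to change.** Replace envelopes opened by the recruiter with an allocation released only once eligibility, consent and baseline data have been entered and locked. Use the electronic trial database if it supports this; Data management describes it only for data entry and storage, so this needs checking. Otherwise let existing staff outside recruitment release the allocation. Keep block sizes undisclosed to everyone who recruits.

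Both parts are needed. Locked release separates the recruiter from the allocation list and leaves a dated record of the order of steps. In an open trial the nurse will still learn past allocations, so undisclosed block sizes are what limit prediction of the next one. Neither part changes the fact that naming Hospital at Home is right 80% of the time at a 4:1 ratio.

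The cost is a small set-up effort, with no additional patients or assessments.

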### Study population

Patients 65 years of age and older who are admitted to the medical ED will be identified by the ED staff as potential eligible patients. Subsequently, the ED staff will inform the research nurse. The research nurse will complete the eligibility criteria checklist (table 1). The research nurse will ask the patient and their informal caregiver (ie, partner, child, relative, friend) for their willingness to participate in the study and to provide written informed consent. The patient and informal caregiver will need to both sign the informed consent form before the patient can participate in the H@H trial.

**Table 1 T1:** Patient eligibility criteria for participation in Hospital at Home trial

Inclusion criteria	Exclusion criteria
Age 65 years of age and older Cognitive impairment, that is, dementia, delirium or other cause of cognitive impairment, and either Previously diagnosed or documented in the medical records or Identified by the ED clinician (eg, with the 4AT test and/or six-item cognitive impairment test)^42–44^ Presented at the ED with a defined acute illness Required hospital admission, according to the attending ED physician but not expected to require emergency interventions, Modified Early Warning Score ≤2 points^45–47^ Living in hospital’s catchment area (<25 km) Informal caregiver is present and able to understand and perform instructions and consented to participate in the trial Home suitable for Hospital at Home care (available informal caregiver, running water, adequate heating, safety)^44^	Previously enrolled Hospitalised within the 7 days preceding ED presentation Nursing home residents or awaiting a nursing home place on an active waiting list (excluding so-called sleeping waiting list candidates)^27^ Additional care needed: Required surgical assessment Suspected acute coronary syndrome or cardiac arrythmia^45^ Dialysis dependent patients^45^ Expected terminal events^45^ or in need of diagnostic or palliative care due to oncological or haematological illness

ED, emergency department.

An evaluation to assess the mental capacity is conducted by the involved ED staff in the setting of the ED assessment. If the participant lacks the capacity to consent (mentally incapacitated), and an informal caregiver (ie, partner, child, friend) is present, this informal caregiver will be asked to act as a personal consultee. The personal consultee will determine whether he or she believes that participation in the study would be in accordance with the values and interests of the individual and will subsequently sign the patient’s informed consent form.

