### Sample size of study population

Based on the numbers available from the ED of the University Medical Center Groningen, the Netherlands, we calculated that an average of 3990 older patients 65 years and over is admitted to our medical ED each year. The Hospital at Home trial will be introduced during working hours, which provides an estimated 1900 patients per year. Not all 1900 patients will be eligible for study inclusion. Based on screening of ED medical records, approximately 15% of the patients meet the eligibility criteria for Hospital at Home care, resulting in 285 eligible persons per year. In recent randomised controlled trials (RCTs) of Hospital at Home care in Italy, 54% and 57% of the eligible patients was willing to participate and gave informed consent.^28 29^ We presume a similar consent rate of 50%, as described in these previous clinical trials, and expect for 143 patients to be included.

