#### Feasibility

For the participation rates, the proportion of participants per step will be calculated. The reasons for non-participation and data concerning the characteristics of non-participants will be collected. We consider the participation rate feasible when it is similar to the participation rate as is described in previous RCTs and around 50% of the eligible patients will consent to participate.^28 29^ Quality of care will be measured by collecting data on patient, institutionalisation (eg, to the hospital or nursing home), mortality, activities of daily living functioning, prevalence of hospitalisation-associated geriatric syndromes, the length of stay in the hospital or Hospital at Home care programme and contact with healthcare professionals. The study is considered feasible if the quality of care of Hospital at Home care on these measurements is non-inferior to usual hospital care.

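### The recruitment criterion tests consent alone, so it can be met at 50% with far fewer than the 143 patients per year that the plan expects

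*Protocol article*

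**What the plan says.** Three sections of the protocol article bear on this.

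- **Study population.** Patients aged 65 and over at the medical ED "will be identified by the ED staff as potential eligible patients". "Subsequently, the ED staff will inform the research nurse", who then completes the eligibility checklist in Table 1 and seeks consent. No other route into the study is described.
- **Sample size of study population.** The projection starts from 3990 older patients a year. Restriction to working hours is the step "which provides an estimated 1900 patients per year". "Based on screening of ED medical records, approximately 15% of the patients meet the eligibility criteria for Hospital at Home care", which gives 285 a year. A 50% consent rate, set beside 54% and 57% in two Italian trials, gives 143 patients.
- **Feasibility.** The participation rate counts as feasible when it resembles that of the previous trials and "around 50% of the eligible patients will consent to participate". Proportions at each step will be calculated, but no threshold is attached to any step other than consent. A separate sentence makes the feasibility of the study depend on non-inferior quality of care.

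**The concern.** Recruitment comes first in the stated primary aim, and the participation rate is the first objective. The expected intake is a product of several factors: attendances, the eligible fraction, identification by ED staff, and consent. The criterion looks only at the last. It would give the same favourable answer whether the trial enrolled all the patients it projected or a small part of them.

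The denominators may also differ. The 285 comes from a records screen. In the trial, eligibility is established only for patients about whom the nurse has been informed. Going from 285 to 143 by consent alone makes no allowance for eligible patients who are not identified. Those patients would also be absent from the non-participation data, which are collected when patient or caregiver withholds consent (Study procedures) and from eligible patients who decline (Process evaluation).

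What is at stake is the recruitment estimate for a future trial. A 50% figure carried forward without the yield behind it could lead that trial to plan for more patients than it can enrol.

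**Working it through.** **Inputs from the article:** 1900 working-hours patients per year, 15% eligible and 50% consent (Sample size of study population); 4:1 allocation (Trial design). **Assumed input:** the share *f* of eligible patients whom ED staff identify. The article gives no figure.

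**Step 1. Reproduce the plan's figures.** 1900 × 0.15 = 285. 285 × 0.50 = 142.5, rounded to 143. Both agree with the article. Because 285 is a yearly figure, 143 is yearly too. The projection implicitly sets *f* = 100%.

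**Step 2. Let identification vary and hold consent at 50%.** Enrolled = 285 × *f* × 0.50. Participation among all eligible patients = enrolled / 285 = *f* × 0.50.

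| *f* (assumed) | Eligible patients seen by the nurse | Enrolled per year | Enrolled as share of 285 | Consent among those seen |
|---|---|---|---|---|
| 100% | 285 | 143 | 50% | 50%, criterion met |
| 75% | 214 | 107 | 37.5% | 50%, criterion met |
| 40% | 114 | 57 | 20% | 50%, criterion met |
| 25% | 71 | 36 | 12.5% | 50%, criterion met |

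At 4:1 the usual-care arm is one fifth of enrolment: about 29, 21, 11 and 7 patients a year in these rows. The quality-of-care condition sets no minimum number either.

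**Step 3. Let the eligible fraction vary instead.** Suppose every eligible patient is identified but only 5% are eligible (assumed). Then 1900 × 0.05 = 95 eligible, and 95 × 0.50 = 47.5, about 48 enrolled. The criterion is again met.

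**Step 4. Can the counts tell the two causes apart?** In the 40% row the nurse sees 114 eligible patients and enrols 57. A true eligible fraction of 114 / 1900 = 6% with complete identification gives the same 114 and 57. The stated steps do not distinguish these cases, although they call for different remedies.

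**The case against.** The strongest reply is that the Study population sentence, read literally, covers everyone aged 65 and over at the medical ED. On that reading the nurse checks them all and the gap between denominators largely closes. The reading is possible, and the case against the criterion does not depend on rejecting it: Step 3 assumes complete identification and the criterion is still met at about 48 patients.

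Several other replies stand in part.

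- The per-step proportions and the CONSORT flow diagram, set beside 285 and 143, would show a shortfall. A reader might infer that the plan could not detect one; that goes too far. What remains is that the participation verdict does not use this information.
- The process evaluation interviews ED physicians and nurses, which could help explain low referral. It would not measure it.
- A reader might infer that ED staff choose whom to refer, or favour families likely to agree, and so inflate the participation rate. The article says only that staff identify patients. Nothing in it supports selective referral, and the calculation needs only incomplete identification.
- The 50% decides the participation-rate criterion, not the feasibility of the whole study, which is also tied to quality of care. A consent-based measure is a coherent way to compare with the earlier trials, so it should be kept.
- A screening log may exist in the full protocol, and the flow chart is not shown. Its absence from the article is therefore not the complaint. A log would not alter the stated criterion.
- A retrospective records screen may not establish that a caregiver was available or the home suitable. This limits one part of the remedy.

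**Conclusion.** The concern holds as a weakness in a stated decision rule. The arithmetic behind 285 and 143 is correct. The participation criterion does not respond to yield: at 50% consent it is met with 143, 107, 57 or 36 enrolled per year as identification falls from 100% to 75%, 40% or 25%, and with about 48 if the eligible fraction is 5%. These shares are assumptions chosen to show the range; the article provides none, and no particular shortfall is predicted. The qualitative result needs only that identification is below 100% or the eligible fraction below 15%.

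The conclusion goes no further than this. A recruitment shortfall would be visible in the reported flow, but it would not affect the participation verdict, and no stated step would separate unidentified eligible patients from a smaller eligible pool. Since recruitment is the first-named aim, the rule should be changed.

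**What to change.** 1. In the Feasibility section, base the recruitment verdict on yield against the plan's own figures (1900 attendances, 285 eligible and 143 included per year) as well as on consent of about 50%. State in advance how far below those figures still counts as feasible.
2. Start the per-step flow from all working-hours medical ED attendances aged 65 and over, followed by patients referred to the nurse, confirmed eligible and consenting.
3. Where feasible, repeat the planning records screen on a sample of periods and report the number apparently eligible on records but not referred. Present it as an upper bound, because records may not show caregiver availability or home suitability.

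The first change needs no new data beyond the counts in the second. The third takes a little research-nurse time and uses a method already applied at planning. The recruitment result may look less favourable. Clinical care and randomisation are unaffected.
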